##### Korean pattern identification questionnaire

2.5.2.5

Qi Blood Yin Yang Deficiency Questionnaire is based on a 4-point Likert scale, composed of 15 questions.^[24]^ It was developed as a tool to assess chronic fatigue, and studies on its validity have been conducted.^[25]^ Measurements are taken at the baseline, 2 weeks, 4 weeks, 6 weeks, and 10 weeks after treatment.

##### Inflammation markers

2.5.2.6

Many researchers have reported changes in the immune and inflammatory responses as a mechanism of CRF and inflammation-related cytokine studies, in relation to CRF, have been conducted.^[26–30]^ In this regard, we aimed to examine the inflammatory markers as one of the objective indicators of the efficacy of Kyung-Ok-Ko in improving fatigue. Inflammatory markers included C-reactive protein, erythrocyte sedimentation rate, and cytokines, such as interleukin (IL)-1, IL-6, tumor necrosis factor (TNF)-α, IL-1ra, IL-8, IL-10, and interferon (IFN)-γ. Measurements are taken at the baseline and 6 weeks after treatment.

### Safety

2.6

AEs refer to undesirable, unintended signs, symptoms, or diseases that occur during clinical trials and do not necessarily have causal relationships with treatments used in the trial. The presence of AEs should be checked at every visit. The severity of AEs will be evaluated by Common Terminology Criteria for Adverse Events (CTCAE). An SAE refers to one of the following AEs occurring in a clinical study participant during a clinical trial:

(1)Death or danger to life;(2)Hospitalization or extension of hospital stay due to the adverse event;(3)Permanent or significant failure or degradation of function;(4)Development of fetal malformations or abnormalities;(5)Other medically important situations.

In the case of SAEs, the investigators should report to the sponsor very quickly (usually within 24 hour). This would ensure patient safety in the clinical trials and meet the reporting requirements of the Korean MFDS. In addition to reporting AEs to the sponsor, the investigator also reports to the Institutional Review Board (IRB). To assess the safety, laboratory tests determined the AST, ALT, alkaline phosphatase, total bilirubin, gamma glutamyl transferase, blood urea nitrogen, and creatinine. Measurements are taken at the baseline, 2 weeks, 4 weeks, 6 weeks, and 10 weeks after treatment.

### Sample size

2.7

The sample size was estimated following a similar clinical research study because the exact same study design has not been employed before. The primary endpoint is the BFI, and the sample size is calculated based on the effect size of the primary endpoint. According to the previous literature,^[31]^ the mean and standard deviation of BFI were 3.4 ± 1.6 and 5.2 ± 1.9 for the experimental group and placebo group, respectively. Using a 0.05 significance level, 90% power, and allowing for a 10% dropout rate, a sample size of 50 participants was estimated, 25 in each group.

### Recruitment

2.8

Among lung cancer patients receiving cancer treatment, patients who experienced CRF are recruited from the division of pulmonology and radiation oncology of the Kyung Hee University Medical Center. This clinical trial is to be conducted at K-CTC. The purpose of this study is explained to the subjects, and screening is conducted among those who signed the informed consent form.

### Data management and monitoring

2.9

Data collection is conducted based on the approved protocol. The collected data is recorded in the case report. The quality of the study will be managed by regular monitoring. An independent monitoring supervisor would be assigned to contact and visit the researchers regularly, and thus, supervise the trial process. All investigators will be trained and will comply with GCP regulations. All documents related to the clinical trial will be archived by the principal investigator and the manager. Data will be stored in a separate place with security. The participants’ information will be maintained in storage for a period of 3 years after study completion. In case of a change in the protocol, it will be immediately reported to the IRB, and all investigators will be informed

### Ethics

2.10

This trial has been authorized by the IRB of the Kyung Hee University Korean Medicine Hospital (KOMCIRB 2018-05-017-001). The protocol complies with both the Declaration of Helsinki and GCP Guidelines. Signed informed consent forms will be obtained from all eligible participants before enrollment.

This trial is registered with the Korean Clinical Trial Registry (KCT0003115).

### Statistical methods

2.11

Statistical significance is based on the significance level 0.05 with a power of 0.8.

ITT: Includes all subjects who were administered with the study drug or placebo at least once, and performed and returned the evaluation sheet for BFI.PP: Includes all subjects who were administered with >80% of the assigned study drug or placebo, and completed the evaluation sheet for at least 34 days (80% of a total of 42 days) of BFI.For all analyses, ITT analysis is the major analysis, and PP analysis is simultaneously performed to present the results together.

Continuous variables are presented as mean and standard deviation, and independent t test or Mann–Whitney *U* test is performed. Categorical variables are presented as frequency and ratio, and Chi-square test or Fisher's exact test (when the expected frequency is less than 5 at 25% of the total value) is performed.

Primary efficacy evaluation is the comparison of the mean of BFI score assessed at week 6 (42 days after administration) between the groups. The mean difference between the baseline and week 6 of VAFS, FACIT-F, MoCA-K, HADS and inflammation markers are to be compared. Independent *t* test is performed if normality test is satisfied, and Mann–Whitney *U* test is performed if the normality test is not satisfied. If a significant difference between groups is found for the baseline values, ANCOVA is performed. The missing value will be replaced by the last measured value of each subject, according to the Last Observation Carried Forward (LOCF) method.

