**Methods::**

This is a randomized, placebo-controlled, patients-assessor blind, parallel-group, single-center clinical trial. Lung cancer patients with CRF, after termination of chemo or radiation therapies, are randomized in a 1:1 ratio to receive either Kyung-Ok-Ko or placebo for 6 weeks. The primary outcome is Brief Fatigue Inventory (BFI). The secondary outcomes include Visual Analog Fatigue Scale (VAFS), Functional Assessment of Cancer Therapy (FACIT) Fatigue scale, Hospital Anxiety Depression Scale (HADS), Montreal Cognitive Assessment Korean version (MoCA-K), and Korean pattern identification questionnaire. Adverse events are evaluated by Common Terminology Criteria for Adverse Events (CTCAE). All outcomes and adverse events are assessed at the baseline, mid-treatment, post-treatment, and at 1-month follow-up.

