### Objective and design

2.1

This is a randomized, placebo-controlled, patients-assessor blind, parallel-group and single-center clinical trial. This study was designed to evaluate the efficacy and safety of Kyung-Ok-Ko in lung cancer patients who have received cancer treatment and are experiencing CRF. The trial will be conducted for a total of 10 weeks, as patients who experienced CRF 2 weeks after completing cancer treatment will take the clinical trial drug for 6 weeks, followed by a 4-week observation period. A flow diagram of the study is presented in Figure 1.

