##### Brief Fatigue Inventory (BFI)

2.5.1.1

The BFI is a tool developed for the fast and simple measurement of fatigue and is widely used in studies.^[19]^ It is composed of 9 questions, with 3 questions for the degree of CRF and 6 questions for the effects of CRF. Each question is scored from 0 to 10 points, where a higher score indicates severe symptoms; 1 to 3 point is mild, 4 to 6 point is moderate, and 7 to 10 point is severe. Measurements are taken at the baseline, 2 weeks, 4 weeks, 6 weeks, and 10 weeks after treatment (Table 1).

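### The per-protocol set requires BFI sheets on at least 34 of 42 days, but the protocol schedules only four BFI assessments by day 42, so the rule cannot be applied as worded

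*Protocol article*

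**What the plan says.** Section 2.11 (Statistical methods) gives the PP set two conditions. The first concerns product intake: "Includes all subjects who were administered with >80% of the assigned study drug or placebo". The second concerns the BFI: the patient must have "completed the evaluation sheet for at least 34 days (80% of a total of 42 days) of BFI".

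Section 2.5.1.1 states the BFI schedule in words: "Measurements are taken at the baseline, 2 weeks, 4 weeks, 6 weeks, and 10 weeks after treatment". The abstract also describes assessment by visit: "All outcomes and adverse events are assessed at the baseline, mid-treatment, post-treatment, and at 1-month follow-up". Section 2.1 gives the time frame: patients "will take the clinical trial drug for 6 weeks, followed by a 4-week observation period". The article nowhere describes a daily BFI or a fatigue diary.

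The primary efficacy evaluation is the "comparison of the mean of BFI score assessed at week 6 (42 days after administration) between the groups". On the roles of the two sets, section 2.11 says that "ITT analysis is the major analysis, and PP analysis is simultaneously performed to present the results together".

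**The concern.** The PP rule counts days and the BFI schedule counts visits. The parenthesis in the rule fixes the unit as days out of a 42-day treatment period, which makes sense only if a sheet is filled in each day. The schedule does not provide for that.

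The PP set is to be analysed and reported alongside ITT for all analyses, so someone will have to replace or interpret the rule before it can be used. The possible interpretations do not all give the same set. With 25 patients planned per arm, moving a few patients in or out could shift a PP result. If the interpretation were settled after outcomes were known, membership could be chosen with knowledge of them.

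**Working it through.** **Inputs.** Treatment period: 42 days (sections 2.1 and 2.11). BFI occasions: baseline and weeks 2, 4, 6 and 10, that is days 0, 14, 28, 42 and 70 (section 2.5.1.1). Threshold: 80%, given as 34 days (section 2.11). Planned sample: 50, 25 per arm (section 2.7).

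**1. The plan's own figure.** 0.80 × 42 = 33.6, rounded up to 34. The figure reproduces, so it comes from a count of days and is not a slip of the pen.

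**2. Sheets the schedule can yield.**
- Days 0 to 42: days 0, 14, 28 and 42, so 4 sheets, of which 3 are after baseline.
- Whole trial: those four plus day 70, so 5 sheets.

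**3. Literal wording.** The rule needs 34. The maximum is 4 by day 42 and 5 overall. Both are below 34, so 0 of 50 patients can qualify.

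**4. Looser readings.** None of these is stated in the article.

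| Reading | What it requires | Week-6 BFI guaranteed? |
|---|---|---|
| BFI follow-up to at least day 34, within treatment | the only scheduled BFI from day 34 to day 42 is day 42 | yes |
| 80% of the 3 post-baseline visits to week 6 | 0.8 × 3 = 2.4, so all 3 | yes |
| 80% of the 4 visits from baseline to week 6 | 0.8 × 4 = 3.2, so all 4 | yes |
| 80% of all 5 visits | 0.8 × 5 = 4.0, so any 4 | no |
| Any sheet on or after day 34, week 10 included | day 42 or day 70 | no |

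The readings confined to the 42-day period all require the week-6 BFI, but they differ on whether a missed week-2 or week-4 visit excludes a patient. The last two rows admit a patient with no week-6 BFI. Section 2.11 replaces missing values by last observation carried forward, so such a patient would enter the PP comparison with an imputed value at the primary time point.

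**5. Reach of the defect.** The ITT definition in section 2.11 also has a BFI condition, but it sets no number of days. The week-6 comparison in the ITT set does not depend on the PP rule.

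**The case against.** The strongest reply is that no sensible analyst would deliver an empty set. The rule was probably meant as follow-up through at least 80% of the treatment period, and on the published schedule that is simply the presence of the week-6 BFI. This is a fair reading and would give a usable set. But the article does not say it. The sentence asks for sheets completed for a number of days, and the wording does not select this reading over the others.

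A second reply is that the stated denominator is 42 days, so counting week 10 is strained. That stands in part: admission without a week-6 BFI arises only under readings that go outside the treatment period, so the spread among plausible sets is narrower than the full table suggests.

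A third reply is that a take-home sheet or a diary may exist in the full protocol, or that a statistical analysis plan may define the set properly. Neither document is shown, so this cannot be excluded. It does not remove the contradiction, because the article fixes both the rule and the schedule, and they conflict. The trial schedule table is not shown either, but section 2.5.1.1 gives the schedule in words and cites that table.

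Two stronger inferences should be resisted. A reader might conclude that the primary result is compromised. It is not, because ITT is the main analysis and does not use the 34-day condition. A reader might also conclude that PP membership will be chosen after the data are seen. The article does not show that: section 2.2 keeps the allocation list with a third party until the trial ends, and an analysis plan may settle the matter earlier. Later redefinition is a risk and not a certainty.

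**Conclusion.** The PP rule in section 2.11 and the BFI schedule in section 2.5.1.1 contradict each other. The rule asks for 34 days of sheets; the schedule provides at most 4 by day 42 and 5 in total. On the literal wording the PP set is empty. On looser readings it is not empty, but its membership depends on which unstated reading is adopted.

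This should be fixed, because a named analysis set that is to be reported beside the main one cannot be formed as written. It is not a fault in the primary analysis. The conclusion assumes that the BFI is collected only at the visits listed in section 2.5.1.1. If a daily BFI is in fact collected, the rule could be applied, and the error would lie in the stated schedule.

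**What to change.** In section 2.11, delete the 34-day condition. Define the PP set as patients who took more than 80% of the assigned product, as already stated, and who have an observed BFI at the week-6 visit. State that membership is fixed before unblinding.

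Nothing more is needed to remove the contradiction. The intake threshold can stay as it is. Visit windows and further exclusions are details that an analysis plan may hold, and use of other fatigue treatments is already covered by the withdrawal criteria in section 2.3.3.

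If the full protocol does include a daily BFI diary, leave the 34-day rule and reconcile section 2.5.1.1 with it instead.

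The cost is one or two sentences and no new data or visits. The article reports recruitment as ongoing; if that is still so, the change can be made before any outcome is compared between arms.

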## Discussion

3

This study is the first research protocol to clarify the efficacy and safety of Kyung-Ok-Ko in CRF in lung cancer patients. Kyung-Ok-Ko is widely used in East-Asian countries, especially Korea, for recovery from fatigue and the reinvigoration of physical strength. In addition, Kyung-Ok-Ko is, clinically, the most frequently used drug to improve CRF. Kyung-ok-ko has been proven to have anti-inflammatory effects in a variety of illnesses.^[16–18]^ A study had demonstrated its effect in lung cancer, and the antifatigue effect has also been studied.^[12,13]^ However, a study to investigate the efficacy and safety of Kyung-Ok-Ko in CRF, which is not easily alleviated, and thus, affects the quality of life and prognosis of cancer patients, is yet to be conducted.

Most of the major causes of CRF are side effects of cancer therapy, and it is commonly found that the fatigue mechanism is associated with inflammation. It has been reported that inflammation occurs because the cytokines affecting the brain induce many neurological, physiological, and behavioral changes, causing fatigue.^[26]^ Observational research has found that fatigue is induced by the presence of inflammatory markers,^[27]^ and a pilot study found that fatigue was improved by blocking TNF-α in cancer patients who had experienced fatigue.^[28]^ Based on the previous studies, which have shown the anti-inflammatory effects of Kyung-Ok-Ko, this research was designed to investigate the effect of Kyung-Ok-Ko in the regulation of inflammatory cytokines to reveal the treatment mechanisms of CRF.

This study has the following strengths. First, we unified only lung cancer to examine the efficacy and safety of Kyung-Ok-Ko in fatigue. Second, the study could contribute to the identification of a mechanism in association with inflammation, which is considered as a fatigue mechanism, by observing cytokine level before and after Kyung-Ok-Ko prescription. Third, we developed a dark-brown placebo paste preparation. To achieve this, the researchers had several meetings and tested various prototypes to develop the placebo. Although it was difficult to match the unique fragrance and viscosity of the traditional Korean medicine, we finally made a similar placebo, which made it possible to “blind” the patients and the researcher. Fourth, the study protocol was established closely following the Guidelines for GCP and the Consolidated Standards of Reporting Trials (CONSORT).

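### Inflammation markers: comparing baseline-to-week-6 differences with no stated transformation, and adjusting for baseline only conditionally, loses power if the markers are right-skewed and the effect is proportional

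*Protocol article*

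**What the plan says.** Section 2.5.2.6 of the Protocol article names nine inflammation markers among the secondary outcomes: CRP, ESR and seven cytokines. On timing it says "Measurements are taken at the baseline and 6 weeks after treatment".

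Section 2.11 puts them under the same rule as the symptom and cognition scales: "The mean difference between the baseline and week 6 of VAFS, FACIT-F, MoCA-K, HADS and inflammation markers are to be compared". The t test applies if normality is met. Otherwise a Mann-Whitney "test is performed if the normality test is not satisfied". ANCOVA enters only when the groups differ significantly at baseline. No transformation is mentioned.

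The Discussion gives the markers a clear role. It lists as a strength that the study may help to identify a mechanism "by observing cytokine level before and after Kyung-Ok-Ko prescription".

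The sample size in section 2.7 is set on BFI alone. The documents claim no power for any marker.

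**The concern.** Blood concentrations are positive, often right-skewed, and often change by a proportion rather than by a fixed amount. If that holds here, the absolute change in a patient scales with that patient's own baseline level. Patients with high baseline values then dominate the spread of the differences, and a proportional effect common to all patients is hard to see.

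The rank fallback protects the error rate but does not remove this problem, because it still ranks absolute differences. The conditional ANCOVA helps little, because in a randomised trial a significant baseline difference is rare, and most analyses would therefore go unadjusted.

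At stake is the mechanism question. A real anti-inflammatory effect is more likely to be missed than it need be with the same samples. In addition, neither a mean absolute change in a skewed marker nor a Mann-Whitney p-value gives a readily interpretable effect size.

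**Working it through.** **1. Evaluable patients per arm.** Section 2.7 gives "the mean and standard deviation of BFI were 3.4 ± 1.6 and 5.2 ± 1.9 for the experimental group and placebo group", and then "Using a 0.05 significance level, 90% power, and allowing for a 10% dropout rate".

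- Pooled SD = √((1.6² + 1.9²)/2) = √3.085 = 1.756. Difference = 5.2 − 3.4 = 1.8.
- Normal approximation: n = 2 × (1.960 + 1.282)² × 1.756² / 1.8² ≈ 20.01, so 21 per arm.
- Exact two-sided t test: power 0.8997 at 21 and 0.913 at 22, so 22 per arm.
- Dropout: 22 / 0.9 = 24.4, so 25 per arm and 50 in total. The plan's figure is reproduced.

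The marker checks therefore use 22 per arm.

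**2. Assumptions for the markers (none is in the document).** Log-normal values; log-SD 0.5 to 1.1; correlation r of log baseline and log week-6 values 0.4 to 0.8; a proportional reduction in the treated arm; two-sided 0.05.

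**3. Methods compared by simulation (2,000 to 3,000 trials per setting where the number was recorded).**

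- Plan: Shapiro-Wilk in each arm, then t test or Mann-Whitney on the untransformed change, with ANCOVA on the untransformed scale if the baseline test is significant.
- Alternative: ANCOVA of log week-6 value on treatment and log baseline.

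**4. Results for a 40% reduction.**

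| log-SD | r | Plan | Log ANCOVA | Loss (points) |
|---|---|---|---|---|
| 0.5 | 0.4 | 71% | 94% | 23 |
| 0.5 | 0.8 | 98% | 100% | 2 |
| 0.8 | 0.4 | 34% | 61% | 27 |
| 0.8 | 0.6 | 46% | 73% | 27 |
| 0.8 | 0.8 | 73% | 92% | 19 |
| 1.1 | 0.6 | 26% | 45% | 19 |
| 1.1 | 0.8 | 45% | 71% | 26 |

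Each power figure carries a standard error of about 1 point. Between runs, the largest loss at 40% came out at about 27 to 31 points.

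**5. Closed-form check of the central case (log-SD 0.8, r 0.6, 40% reduction).** The effect is |ln 0.6| = 0.511, and √(2/22) = 0.3015.

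- Log ANCOVA: residual SD = 0.8 × √(1 − 0.36) = 0.640. Ratio = 0.511 / (0.640 × 0.3015) = 2.65. Power ≈ Φ(2.65 − 2.02) ≈ 73%.
- t test on the log ratio: SD = 0.8 × √(2 × 0.4) = 0.716. Ratio = 0.511 / (0.716 × 0.3015) = 2.37. Power ≈ Φ(2.37 − 2.02) ≈ 64%.

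Both agree with the simulation. The gain over 46% thus splits into 64 − 46 = 18 points from the log scale and 73 − 64 = 9 points from baseline adjustment.

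**6. Smaller effects, r 0.6, log-SD 0.5 / 0.8 / 1.1 (plan vs log ANCOVA).**

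- 30% reduction: 60 vs 82%, 29 vs 45%, 16 vs 24%.
- 20% reduction: 31 vs 43%, 13 vs 19%, 9 vs 10%.
- 10% reduction: 11 vs 13%, 6 vs 8%, 7 vs 8%.

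The 10% power in the last 20% setting looks low by simulation error. The formula in step 5 gives 0.223 / (1.1 × 0.8 × 0.3015) = 0.84 and Φ(0.84 − 2.02) ≈ 12%, so the loss there is about 3 to 4 points rather than 1. Over all the assumed SDs and correlations, the loss is about 4 to 13 points at 20% and 9 to 26 at 30%.

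**7. Null case.** The planned rule, with its conditional ANCOVA, rejects in about 4.7 to 4.9% of trials and log ANCOVA in about 5%. Including the conditional ANCOVA changes the plan's power by about 2 points or less.

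**The case against.** The strongest reply is that the planned method is valid, has a rank fallback, and serves only secondary outcomes for which no power is claimed. On this view a more efficient test is a preference, and transformations and assay-limit rules belong in an analysis plan that is not shown. Part of this stands. The error rate is sound, and that the scale is untransformed is inferred from the absence of any stated transformation. But section 2.11 does name the endpoint, the tests and the condition for adjustment. An analysis plan with routine log-scale adjustment would depart from that text, not merely complete it.

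It is also fair that the log-normal, proportional model favours log ANCOVA, and that no passage supports a 30 or 40% reduction. For that reason the size is given as a range that includes small effects.

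Four stronger readings might be inferred, and the documents do not support them:

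- **A loss of 27 points, or of at most 27.** That figure belongs to particular assumed inputs with a 40% reduction. It is neither an estimate for this trial nor a ceiling. With log-SD 0.3 to 1.2, r 0.3 to 0.9 and effects set to give log ANCOVA about 80% power, the loss runs from about 6 to 40 points.
- **No use of baseline as a covariate.** Section 2.11 has a conditional ANCOVA. It recovers little, but it is there.
- **A missed effect would be due to scale alone.** Log ANCOVA itself reaches only 45% at log-SD 1.1, r 0.6 and a 40% reduction. The small sample matters too, and part of the gain comes from baseline adjustment.
- **All nine markers need the log scale.** The documents give no distribution for any of them, and a marker near normal on its original scale would gain little from it.

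**Conclusion.** The point holds as one of efficiency, not validity. If the markers are right-skewed and the effect is proportional, the rule in section 2.11 gives up power on the mechanism question that the same samples could supply. Under the stated assumptions the loss is about 4 to 13 points for a 20% reduction, 9 to 26 for 30% and 2 to 31 for 40%. It is about 1 to 2 points for a 10% reduction at r 0.6, and about 2 points where power is near its ceiling. Every marker input is an assumption; only the 22 per arm follows from the document. The primary BFI comparison is not affected.

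**What to change.** In section 2.11, give the markers their own sentence:

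- Analyse each marker by ANCOVA of the log week-6 value on treatment and log baseline value, in all cases and not conditional on a baseline test. Report the ratio of geometric means (Kyung-Ok-Ko to placebo) with a 95% CI.
- State a substitution rule for values below the assay limit, for example half the limit.
- For a marker with many undetectable values, add Mann-Whitney on the log ratio as a sensitivity analysis.
- A marker close to normal on its original scale may stay untransformed, with the same baseline adjustment. That choice should be fixed before unblinding.

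The cost is one or two sentences and a little programming. Both measurements are already scheduled and no further patients are needed. The downside is that effects are reported as ratios and that undetectable values need the substitution rule. The article reports recruitment as ongoing, so, on that status, the change can be made before unblinding.

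### Whether the primary week-6 BFI analysis uses baseline BFI, and which test it uses, is left to preliminary significance tests; one pre-specified ANCOVA would gain precision at no cost

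*Protocol article*

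**What the plan says.** All the relevant rules are in the protocol article, section 2.11 (Statistical methods).

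- **Primary comparison:** "Primary efficacy evaluation is the comparison of the mean of BFI score assessed at week 6", that is, raw week-6 scores, neither adjusted for baseline nor expressed as change.
- **First switch:** an independent t test is used if normality holds. For Mann–Whitney U the condition reads "test is performed if the normality test is not satisfied". This sentence follows the one on secondary outcomes. Applying it to the primary outcome as well is the natural reading, but it is a reading.
- **Second switch:** "If a significant difference between groups is found for the baseline values, ANCOVA is performed".

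Section 2.5.1.1 has BFI measured at baseline and at weeks 2, 4, 6 and 10, so the covariate is collected anyway. The listed secondary scales and inflammation markers are compared as differences between baseline and week 6, so baseline enters those analyses. No section gives an unconditional baseline-adjusted analysis of the primary outcome.

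**The concern.** Allocation is randomised 1:1 (section 2.2), so any baseline difference between arms is due to chance. A significance test of that difference does not show whether adjustment is worthwhile. That depends on how strongly baseline BFI predicts week-6 BFI. The rule therefore ignores a probably prognostic covariate in most realisations of the trial and leaves an imbalance just short of significance uncorrected.

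The normality switch raises a different problem. Mann–Whitney does not compare means, so a failed normality test changes the quantity being tested away from the stated primary comparison.

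The rules are also incomplete. The protocol does not say which prevails when normality fails and baseline differs. It refers to baseline values in the plural, so neither the trigger nor the covariate set is fixed. At stake are precision in a 50-patient trial and a primary result with one meaning fixed in advance.

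**Working it through.** **Inputs from the protocol.** Section 2.7 takes its effect from an earlier study: "mean and standard deviation of BFI were 3.4 ± 1.6 and 5.2 ± 1.9" (active arm first). Its design settings are level 0.05, power 90% and dropout 10%, and its result is 50 patients, 25 per arm.

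**Assumptions, not in the protocol.** Two-sided testing; correlation r between baseline and week-6 BFI of 0.3, 0.5 or 0.7; a smaller true difference of 1.2 points as an alternative; normal data.

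**1. Reproduce the sample size.**
- Difference: 5.2 − 3.4 = 1.8.
- Pooled SD: √[(1.6² + 1.9²)/2] = √3.085 = 1.756, so d = 1.8/1.756 = 1.02.
- Normal approximation: n = 2(1.960 + 1.282)² × 3.085/1.8² = 20.01, rounded up to 21 per arm; 21/0.9 gives 24.
- Noncentral t: 22 per arm; 22/0.9 = 24.4, giving 25 per arm and 50 in total, the stated figure.

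The trial is therefore sized for an unadjusted comparison at 90% power. The power of 0.8 mentioned in section 2.11 gives only 17–18 per arm after dropout. That conflict is a separate matter.

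**2. How often the baseline rule applies.** With baseline BFI as sole trigger at 0.05, ANCOVA is used in 5% of trials (simulated: 4.9–5.1%) and not used in 95%. If any of five independent baseline variables could trigger it, the chance is 1 − 0.95⁵ = 23%.

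**3. Precision in principle.** The unadjusted standard error with 22 per arm is 1.756 × √(2/22) = 0.53. ANCOVA multiplies the variance by 1 − r², that is 0.91, 0.75 or 0.51. The standard error falls by about 5%, 13% or 29%.

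**4. Simulation of the written rule.** Baseline t test at 0.05, ANCOVA if significant, otherwise t test; 22 per arm, 100,000 trials per scenario.

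| | r = 0.3 | r = 0.5 | r = 0.7 |
|---|---|---|---|
| SD of estimate, written rule | 0.52 | 0.51 | 0.49 |
| SD of estimate, always ANCOVA | 0.51 | 0.46 | 0.38 |
| Type I error, written rule | 4.9% | 4.5% | 3.7% |
| Power at 1.8, written rule | 91.5% | 92.1% | 92.8% |
| Power at 1.8, always ANCOVA | 93.1% | 96.6% | 99.6% |
| Power at 1.2, written rule | 59.8% | 60.5% | 61.6% |
| Power at 1.2, always ANCOVA | 62.8% | 71.2% | 86.2% |

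A separate run of 40,000 trials agrees within about one percentage point: type I error 4.9/4.3/3.6%; power at 1.8 points 91/92/93% against 93/97/99.6%; power at 1.2 points about 61% against 63/72/86%.

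**5. Normality switch.** The protocol names no test. A Shapiro–Wilk test at 0.05 in each arm would divert 1 − 0.95² = 9.75% of truly normal trials to Mann–Whitney (simulated: 9.4–10.1%). Adding this step changed power by at most about 0.3 percentage points.

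**6. Conditional error given an imbalance.** Given baseline z, the unadjusted outcome statistic under the null has mean r·z and variance 1 − r². The chance that it exceeds 1.96 in absolute value is:

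| Baseline z | r = 0.3 | r = 0.5 | r = 0.7 |
|---|---|---|---|
| 1.0 | 5.0% | 4.8% | 3.9% |
| 1.5 | 6% | 8% | 10% |
| 1.9 | 8% | 12% | 19% |

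Only about 0.7% of randomised trials have |z| between 1.90 and 1.96.

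**7. Effect of the entry rule.** Entry requires BFI of at least 4 (section 2.3.1), which narrows the baseline range. If truncation leaves a fraction v of the baseline variance, r becomes r√v/√(1 − r² + r²v). For an assumed normal baseline with SD 1.756, a mean of 4 gives v = 0.363 and a mean of 6 gives v = 0.671. An underlying r of 0.5 then falls to 0.33–0.43, and 0.7 to 0.51–0.63.

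**The case against.** The strongest defence is that the plan as written is a valid test. A reader might infer that choosing the analysis from the data inflates the false-positive rate. It does not: overall type I error is about 3.6–4.9%, slightly conservative. A reader might also infer that the trial is underpowered. Under its own assumptions it is not: the sample size reproduces for an unadjusted comparison, and the written rule keeps 91–93% power at 1.8 points, above the 90% target.

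The conditional error of 12–19% at z = 1.9 is arithmetically right but describes an edge case. It should not be read as the trial's error rate. The 95% figure holds only if baseline BFI is the sole trigger. The precision gain is negligible at r = 0.3, the 1.2-point effect is an assumption of this review, and the entry rule may push the correlation down. The normality switch costs almost no power.

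All of this stands, and it limits the size of the point. It does not justify the rule itself: the baseline test still does not indicate when adjustment helps, the two switches still lack a defined combination, and in every scenario examined ANCOVA throughout was at least as precise and powerful.

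**Conclusion.** The point holds as an efficiency and specification weakness of moderate priority, not as a validity failure. The primary method is set by preliminary tests, and baseline BFI usually goes unused although it is collected.

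At the planned effect the power forgone runs from about 2 percentage points (r = 0.3) to about 7 (r = 0.7). At an assumed 1.2-point effect it runs from about 3 to about 25. These figures rest on 22 evaluable patients per arm, normal data, a two-sided 0.05 level, baseline BFI as sole trigger and an assumed correlation. The protocol supplies no correlation, and the BFI entry threshold makes the upper end of the range less likely. A chance imbalance short of significance would go uncorrected, although large imbalances of that kind are rare.

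**What to change.** In section 2.11, replace the two conditional rules for the primary outcome with one analysis: ANCOVA of week-6 BFI on treatment with baseline BFI as covariate, reporting the adjusted mean difference with its 95% confidence interval whatever the baseline or normality results. Drop the baseline significance test and the normality test as decision rules. Keep Mann–Whitney or rank ANCOVA as a named sensitivity analysis. Using the same model for the secondary scales, which are already analysed as change from baseline, is optional.

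The cost is a few sentences of wording, with no new data and no more patients. The article reports recruitment as ongoing, so the change should be made and dated before unblinding.
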